#### Drop-out criteria

3.2.5

Investigator-determined withdrawal: ① Occurrence of a serious adverse event (SAE) leading to trial discontinuation based on investigator judgment; ② Development of a new severe intercurrent illness that may confound efficacy or safety assessments.

Subject-initiated withdrawal: ① Voluntary withdrawal from the trial for any reason; ② Loss to follow-up, defined as failing to receive the intervention or complete assessments for two consecutive scheduled visits despite attempts to make contact.

Handling of Drop-out Cases: ① The investigator will attempt to contact the subject to document the reason for dropout and the last intervention date, and to complete any feasible assessments; ② Subjects who dropout due to adverse events will receive appropriate clinical management; ③ All data from dropout cases will be preserved and included in the intent-to-treat (ITT) analysis.

### Sample size estimation

3.3

The sample size for this study was calculated using the standard formula for comparing means between two independent groups in a randomized controlled trial. The formula and parameters are defined as follows: Sample Size Calculation Formula:

$$\begin{array}{c} n=2\times {\left[\frac{\left(Z_{\alpha /2}+Z_{\beta /2}\times \sigma \right)}{\Delta }\right]}^{2} \end{array}$$
(1)

Where: *n* = sample size per group; *Z*_α_/2 = critical value for a two-tailed test at significance level α; *Z*_β_ = critical value for Type II error rate β; σ= population standard deviation of the primary outcome; Δ = minimum clinically important difference.

Basis for Parameter Setting: *Z*_α_/2: A two-tailed significance level (α) of 0.05 was used, corresponding to *Z*_α_/2 = 1.96; *Z*_β_: A statistical power (1 – β) of 80% was targeted (β = 0.2), corresponding to *Z*_β_ = 0.84; Δ and σ: Based on previous taVNS randomized controlled trials (17–19) and our pilot data, we assumed a continuous primary outcome (e.g., postoperative quality of life score or change in serum IL-6). The expected between-group difference (Δ) was three points, with a common standard deviation (σ) of five points.

Sample Size Calculation Result: Using the above parameters, 22 participants were required per group, yielding an initial total sample size of 44. Accounting for an anticipated 10% dropout rate, the final sample size was increased to 50 participants. These will be randomly assigned at a 1:1 ratio to the intervention (taVNS, *n* = 25) and control (sham stimulation, *n* = 25) groups.

Power analysis was performed for the primary outcomes (gut microbiota and brain function). The final sample size ensures ≥80% power for both. This sample size also covers the secondary endpoints and no separate calculation was needed.

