
The innovations of this study are reflected in three aspects: First, the combination of taVNS and the GBA theory is applied to the postoperative management of AD for the first time, overcoming the limitations of traditional single-system interventions by regulating complications through the synergistic actions of neural, immune, and endocrine pathways. Second, a multidimensional outcome indicator system is utilized, which includes not only core GBA biomarkers such as gut microbiota diversity and inflammatory factors but also, through collaboration with the rehabilitation department, real-time monitoring of brain function changes via BCI and fNIRS, enabling cross-system correlation analysis of intestinal function, inflammation, and brain function in postoperative patients. Third, a randomized controlled design is strictly followed: a sham stimulation control (with no current output, targeting non-vagus nerve innervated areas) is implemented, and stratified randomization based on the Stanford classification is employed to reduce bias and enhance the reliability of the results.

From a methodological perspective, the intervention protocol in this study is rigorously designed. For taVNS, the stimulation sites are selected as the cymba conchae or tragus (areas rich in the auricular branches of the vagus nerve), and the parameters are set to a frequency of 15 Hz and a pulse width of 200 μs—based on international standards and previous anti-inflammatory research evidence—to ensure the stimulation intensity is within patients' tolerance range while effectively activating the vagus nerve pathway. The sample size estimation is based on effect sizes of gut microbiota and inflammatory factor changes reported in similar studies; after accounting for a 10% dropout rate, 25 cases per group were determined, meeting statistical power requirements. The procedures for collecting and processing biological specimens (e.g., fecal samples stored at −80 °C, metagenomic sequencing for gut microbiota structure analysis) are standardized, and analyses are conducted by third-party laboratories to ensure data objectivity.

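### The stated sample-size inputs require 44 patients per group, not 22, so power for the target difference is about 49–55% rather than 80%

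*Protocol article*

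**What the plan says.** Section 3.3 (Sample size estimation) bases the calculation on the "standard formula for comparing means between two independent groups in a randomized controlled trial" and defines n as the "sample size per group". Its inputs are:

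- Type I error: "A two-tailed significance level (α) of 0.05 was used", with Z = 1.96.
- Power: a level "of 80% was targeted", with Z = 0.84.
- Effect and spread: "The expected between-group difference (Δ) was three points, with a common standard deviation (σ) of five points".

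The result is given as: "Using the above parameters, 22 participants were required per group, yielding an initial total sample size of 44". A 10% dropout allowance raises this to 50, or 25 per group. The section then asserts that the final number gives at least 80% power for both primary outcomes (gut microbiota and brain function) and is also enough for the secondary endpoints. The Discussion (section 4) repeats the assurance: "25 cases per group were determined, meeting statistical power requirements".

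**The concern.** The method, the meaning of n, every input and the result are all printed, and they do not agree. A standardised difference of 3/5 = 0.6 needs roughly twice as many patients per group as the plan states.

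The sample-size section is the only justification for the size of the trial. If it stands, the trial will be reported as having 80% power when it has about an even chance of detecting the difference it was designed to find. A null result could then be taken as evidence of no effect, when missing a true 3-point difference would be nearly as likely as finding it.

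**Working it through.** **Inputs (all from section 3.3).** Z for two-sided α = 0.05: 1.96. Z for 80% power: 0.84. Δ = 3, σ = 5. Two independent groups, 1:1, n per group, dropout 10%.

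**Where 22 could come from.**

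- Without the leading factor 2: [(1.96 + 0.84) × 5/3]² = 4.667² = 21.8, rounded up to 22. This is the one-sample form and does not suit a two-group comparison.
- The same figure results if the correct per-group answer of 44 is taken as the total and divided by two. The document does not show which happened, and the consequence is the same.
- The later steps are consistent with 44 as the total: 44/0.9 = 48.9, so 49, stated as 50.

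**The named formula with the stated inputs.**

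n = 2 × [(Z_α/2 + Z_β) × σ/Δ]² = 2 × 21.78 = 43.6, so 44 per group and 88 in total. The exact t-test calculation gives 45 per group. With 10% dropout, 88/0.9 = 97.8, so 98 in total.

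**Other readings tried.**

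| Reading | n per group |
|---|---|
| Equation (1) as printed (σ on the second term only), second Z = 0.84: 2 × [(1.96 + 0.84 × 5)/3]² | 8.4 |
| Equation (1) as printed, second Z = 1.28 (Z_β/2 taken literally) | 15.6 |
| Standard formula with Z_β/2 = 1.28 | 58.4 |
| Standard formula, one-sided α = 0.05 | 35 |

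None gives 22. Equation (1) also differs from the section's own definitions: it prints Z_β/2 where the text defines Z_β, and its bracket leaves Z_α/2 unmultiplied by σ.

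**Power at the planned size (Δ = 3, σ = 5, two-sided α = 0.05).** The noncentrality is 0.6 × √(n/2).

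| n per group | Noncentrality | Power, normal approximation | Power, t-test |
|---|---|---|---|
| 22 | 0.6 × √11 = 1.99 | 51.2% | 49.4% |
| 25 | 0.6 × √12.5 = 2.12 | 56.4% | 54.7% |
| 44 | 0.6 × √22 = 2.81 | 80.4% | 79.5% |
| 45 | 0.6 × √22.5 = 2.85 | 81.2% | 80.4% |

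**Difference detectable with 80% power (t-test).**

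- 22 per group: d = 0.865, and 0.865 × 5 = 4.3 points.
- 25 per group: d = 0.809, and 0.809 × 5 = 4.0 points.

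**Sensitivity to the planned α.** Section 3.9.1 tests the primary outcome at a Bonferroni-corrected α of 0.01. At that level the same inputs need 65 per group. Power is then 25% (t-test) to 28% (normal) with 22 per group, and 30% to 32% with 25.

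**The case against.** The strongest counter-argument is that about 50% power describes an unadjusted two-group comparison at α = 0.05 of an illustrative outcome. Section 3.3 offers quality of life or change in IL-6 as examples, and both are secondary outcomes. The claim of at least 80% power concerns gut microbiota and brain function. The planned analysis is a repeated-measures mixed model (section 3.9.2), which can be more efficient than a single comparison of means.

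Part of this stands: the recalculation shows that 22 does not follow from the stated inputs, but it does not establish the power for the microbiota or brain-function measures. It does not rescue the plan, however. No other inputs are printed for those outcomes, so the 80% claim has no visible support. Section 3.3 claims no gain from baseline adjustment or repeated measures. For baseline adjustment to make 22 per group sufficient, 1 − ρ² would have to equal 22/43.6, a correlation of about 0.70, and none is stated. The corrected α of 0.01 pulls the other way.

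Two smaller objections are fair. The faults in equation (1) may be typesetting, since the text makes the intended formula clear; the finding does not depend on them. The Discussion does concede a relatively small sample, but it limits the power concern to subgroup analyses, including rare adverse events, and leaves the main claim standing. Nor is this an effect of condensing a longer protocol, because the formula, inputs and result are all given.

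**Conclusion.** The error is established from the document alone. The stated inputs require 44 per group (88 evaluable, about 98 with 10% dropout), and the plan has 22 per group (44 evaluable, 50 randomised). At Δ = 3, σ = 5 and two-sided α = 0.05, t-test power is 49% with 22 per group and 55% with 25. The normal approximation gives 51% and 56%.

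These figures assume an unadjusted comparison of two independent means, as section 3.3 specifies. They are favourable relative to the α of 0.01 planned for the primary outcome. This must be corrected, because the assurances of 80% power in section 3.3 and in the Discussion are unsupported by the only calculation shown.

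**What to change.** Keep 50 patients and correct the text:

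1. In section 3.3, print n = 2[(Z_α/2 + Z_β)σ/Δ]² and its result, 44 per group and 88 in total.
2. State that 50 randomised (50 × 0.9 = 45 evaluable) gives about 50% power for Δ = 3 and σ = 5 at two-sided α = 0.05, or 80% power only for a difference of about 4.3 points. Name the α beside the power, and give the lower figure at 0.01 if that remains the level for the primary outcome.
3. Remove the statement of at least 80% power for both primary outcomes and the statement that the number covers the secondary endpoints. Remove the matching assurance in the Discussion.
4. Label the trial exploratory, with estimates and confidence intervals as the main result.

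Enlarging the trial to about 98, or documenting a different Δ, σ or baseline correlation, would also resolve the contradiction. The first of these needs 98 − 50 = 48 more patients.

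The recommended route costs wording only, in the protocol and in the registry record if that repeats the claim. The stated power becomes less favourable and no patients are added.

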#### Secondary outcome measures

3.6.2

① Inflammatory Markers: Serum IL-6 and TNF-α levels will be measured via enzyme-linked immunosorbent assay. IL-6 is a key pro-inflammatory cytokine involved in systemic inflammation, and elevated levels correlate with vascular wall damage and organ dysfunction. TNF-α induces vascular endothelial cell apoptosis and promotes inflammatory cytokine cascades, with its levels positively correlating with the severity of postoperative inflammation in AD patients. Both markers will be used to evaluate the anti-inflammatory effect of taVNS.

② Neurotransmitters: Serum levels of 5-HT and BDNF will be measured via enzyme-linked immunosorbent assay. 5-HT is a critical neurotransmitter in both the central and peripheral nervous systems, involved in mood regulation and intestinal motility; reduced levels are associated with anxiety, depression, and gastrointestinal dysfunction. BDNF promotes neuronal survival, synaptogenesis, and neuroplasticity, and is closely linked to cognitive function and neural repair; low levels indicate impaired neural regeneration. These neurotransmitters will be used to evaluate taVNS-mediated regulation of the neuroendocrine system.

③ Intestinal Function: Bowel sound frequency will be recorded by auscultating periumbilical sounds every 4 h (normal range: 4–5 times per minute; reduced frequency indicates slowed intestinal peristalsis, while hyperactivity suggests intestinal irritation). The time to first postoperative spontaneous flatus and defecation will also be recorded (delays indicate impaired intestinal function recovery and serve as a direct marker of gastrointestinal dysfunction). These parameters will be used to comprehensively assess postoperative intestinal motility and function in AD patients.

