#### Data collation

3.9.1

Data will be collected using CRFs, capturing baseline characteristics, intervention records, laboratory results, and scale scores. All biological specimens will be de-identified via unique codes to protect participant privacy. Statistical analyses will be performed using SPSS 22.0, with the following approach:

① Statistical Tests by Data Type: Categorical variables will be summarized as frequencies (percentages) and compared using the chi-square test. Continuous variables will be presented as mean ± standard deviation; after testing for normality and homogeneity of variance, parametric data will be analyzed using *t*-tests (independent or paired, as appropriate), while non-parametric data will be analyzed using the Mann–Whitney *U* test (rank-sum test). Ordinal data (e.g., scale scores) will also be analyzed using non-parametric rank-sum tests.

② Analysis of Primary and Secondary Outcomes: Outcomes include scale scores (GIDS, HAMA, HAMD, SF-36, and PSQI), brain function parameters (EEG, fNIRS-derived rCBF), gut microbiota metrics (diversity indices, taxon abundance), and biochemical markers (IL-6, TNF-α, 5-HT, and BDNF). A stratified multiple comparison adjustment will be applied: the primary outcome will use Bonferroni correction (corrected α = 0.01, accounting for five indicators), while secondary outcomes and biomarkers will use the False Discovery Rate (FDR) method (FDR = 0.05). Subgroup analyses (e.g., by gender, Stanford type) will also employ FDR correction to control Type I error inflation.

③ Correlation Analysis: Multiple linear regression will be used to explore associations between clinical outcomes, gut microbiota, inflammatory markers, and brain function.

④ Significance Level: A two-sided *P* value < 0.05 will be considered statistically significant for all tests, unless otherwise specified after multiplicity adjustment.

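### The statement of at least 80% power for both primary outcomes is unsupported: the only calculation shown uses α = 0.05 and secondary endpoints, while the primary outcome is tested at α = 0.01

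*Protocol article*

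**What the plan says.** Section 3.3 (Sample size estimation) sets the error rates: "A two-tailed significance level (α) of 0.05 was used" and "A statistical power (1 – β) of 80% was targeted (β = 0.2". On the endpoint it says "we assumed a continuous primary outcome (e.g., postoperative quality of life score or change in serum IL-6", and on the effect, "The expected between-group difference (Δ) was three points, with a common standard deviation (σ) of five points". It arrives at 22 per group, raised to 25 per group (50 in total) for 10% dropout. It then reports that a power analysis was done for gut microbiota and brain function, and concludes: "The final sample size ensures ≥80% power for both".

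Three other places bear on this:

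- Section 3.6.1 names gut microbiota and brain function (EEG/BCI and fNIRS) as the main outcomes. Section 3.6.2 lists IL-6 as secondary ("Inflammatory Markers: Serum IL-6 and TNF-α levels will be measured via enzyme-linked immunosorbent assay"), along with the SF-36, the quality-of-life scale.
- Section 3.9.1 (Data collation) states: "the primary outcome will use Bonferroni correction (corrected α = 0.01, accounting for five indicators".
- The Discussion says: "The sample size estimation is based on effect sizes of gut microbiota and inflammatory factor changes reported in similar studies". It adds that 25 per group satisfies the power requirement.

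**The concern.** The power statement is about one set of outcomes tested at one level. The calculation behind it is about other outcomes at a less strict level. A sample size derived at α = 0.05 does not carry its power over to a test at α = 0.01. A difference of three points with an SD of five points is also not on the scale of a Shannon index, a taxon abundance, a P300 latency or an oxyhemoglobin change.

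The statement is the stated justification for 50 patients. A reader who accepts it would take a null primary result as fair evidence against an effect of the assumed size. The limitations in the Discussion concede low power only for subgroup analyses, which there include rare adverse events and Stanford type comparisons. Nothing warns the reader about the main comparison.

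**Working it through.** **Inputs.** From section 3.3: Δ = 3, σ = 5, so d = 3/5 = 0.6; two-sided α = 0.05 (Z = 1.96); power 80% (Z = 0.84); 22 per group before dropout and 25 after. From section 3.9.1: α = 0.05/5 = 0.01 for the primary outcome.

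**Step 1: the plan's own figure.** The usual formula is n per group = 2 × [(Zα/2 + Zβ) × σ/Δ]². With the inputs, 2 × [(1.96 + 0.84) × 5/3]² = 43.6, so 44 per group. The stated 22 does not reproduce. It equals the same expression without the leading 2 (21.8), or 44 per group read as a total. The dropout step does reproduce: 44/0.9 = 48.9, so 49, or 25 per arm and 50 in all.

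**Step 2: power at the disclosed effect.** For a two-sample t-test the noncentrality is d × √(n/2), with 2n − 2 degrees of freedom. That is 0.6 × √11 = 1.99 for n = 22, 0.6 × √12.5 = 2.12 for n = 25, and 0.6 × √22 = 2.81 for n = 44.

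| n per group | α = 0.05 | α = 0.01 |
|---|---|---|
| 22 | 49% | 25% |
| 25 | 55% | 30% |
| 44 | 79% | 57% |

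The normal approximation gives 51% and 56% at α = 0.05, and 28% and 32% at α = 0.01, for 22 and 25 per group.

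**Step 3: separating the two causes.** The first two rows of the table mix the arithmetic error with the α mismatch. Two checks isolate the mismatch:

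- Suppose the true effect is just large enough for 22 per group to give exactly 80% at α = 0.05. By t-test this is d = 0.865. At α = 0.01 the same effect gives 57% with 22 per group and 65% with 25.
- Suppose instead that the arithmetic is put right at 44 per group with d = 0.6. At α = 0.01 the power is again 57%.

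**Step 4: what 80% at α = 0.01 would need.** With d = 0.6, it needs 67 per group by t-test (65 by the normal approximation). With the planned size, the detectable d is 1.07 at 22 per group and 1.00 at 25.

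**Step 5: allowance for the planned model.** Section 3.9.2 uses repeated-measures mixed models, which may gain precision from the baseline. The document gives no correlation. As an assumption, take baseline adjustment with r from 0.5 to 0.7, which divides d by √(1 − r²). Then d becomes 0.6/0.866 = 0.69 to 0.6/0.714 = 0.84. Power at α = 0.01 runs from 36% (r = 0.5, n = 22) to 61% (r = 0.7, n = 25).

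**The case against.** The strongest reply is that section 3.3 reports a power analysis for the two primary outcomes, and that an article may leave its inputs to the full protocol. This stands in part. A reader might infer from the table that power for the primary outcomes is 25–30% and that the 80% statement is therefore shown to be false. The documents do not support that. The value d = 0.6 belongs to a quality-of-life or IL-6 endpoint. No effect size or SD for a microbiota, EEG or fNIRS variable is disclosed, so power for those outcomes cannot be recomputed. The 25–30% is conditional on the only effect the plan gives. What does not stand is treating the point as a mere omission: the article makes a specific quantitative claim, and the calculation beside it is for other endpoints at another α.

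A reader might also attribute the whole drop from 80% to 25–30% to the change in α. That is too strong, because the factor-of-two error already brings power to 49–55% at α = 0.05. The mismatch by itself accounts for a fall from 80% to about 57%, or to 65% with 25 per group.

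Two smaller points are fair. Section 3.9.1 does not name its five indicators. The sentence before lists five scale scores among the outcomes, and section 3.6.1 contains more than five metrics, so which tests carry 0.01 is not clear. The text nevertheless assigns that level to the primary outcome. The Discussion's basis also conflicts only partly with section 3.3: IL-6 is an inflammatory factor and is given there as an example. The microbiota effect sizes are the part with no counterpart in section 3.3.

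**Conclusion.** The point holds as an internal contradiction with an unsupported claim. The statement of at least 80% power for both primary outcomes has no disclosed input for either outcome, and it conflicts with the test level in section 3.9.1. The conflict survives every favourable adjustment tried here: a larger effect that gives exactly 80% at α = 0.05 with 22 per group (57–65%), a corrected 44 per group (57%), and baseline adjustment at an assumed r of 0.5–0.7 (36–61%). For the claim to hold by two-sample t-test at α = 0.01 with 22–25 per group, effects of about 1.00–1.07 SD would be needed in both domains, against the 0.6 assumed.

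These figures assume a single comparison per indicator, and the 36–61% also rests on the assumed correlation. The statement needs correcting because the trial's size rests on it.

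**What to change.** In section 3.3, remove the statement of at least 80% power and the quality-of-life/IL-6 basis. Name one variable in each primary domain. For each, give the expected effect and the SD of the quantity actually analysed, for example from the pilot data the section mentions. An SD from Visit 2 alone would not serve automatically: it is a pre-intervention SD and need not match that of day-7 or change values.

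Then state the power or detectable difference for 22–25 per group at the α that section 3.9.1 applies. At α = 0.01 the detectable d is about 1.00–1.07 by t-test. Keep that α consistent with the number of primary tests, and name the indicators it covers. Bring the Discussion into line, both on the basis of the sample size and on the claim that power requirements are met.

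The cost is one recalculation and some rewording. The stated power becomes less favourable. No extra patients or procedures are needed.

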#### Main statistical models

3.9.2

Mixed-effects models will serve as the core analytical framework to handle repeated measures collected at 1 day, 7 days, 4 weeks, and 24 weeks postoperatively. ① A linear mixed-effects model will be used for continuous outcomes, including gut microbiota indices (Shannon index, Bifidobacterium abundance), brain function parameters (fNIRS rCBF, EEG α-wave power), and biochemical markers (IL-6, TNF-α, 5-HT, and BDNF). ② A logistic mixed-effects model will be applied to binary outcomes, such as adverse events (SAE, skin allergy) and intestinal function recovery (first flatus within 48 h, first defecation within 72 h). ③ An ordinal logistic mixed-effects model will be used for ordinal outcomes, including scale scores (GIDS, HAMA, and HAMD).

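### The statement that the sample size also covers the secondary endpoints describes a property the design does not have: not at the plan's own inputs, not under its FDR rule, and not for its binary endpoints

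*Protocol article*

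**What the plan says.** The Sample size estimation section (3.3) contains one calculation, a comparison of two means. Its inputs are:

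- Significance level: "A two-tailed significance level (α) of 0.05 was used".
- Power: "of 80% was targeted".
- Effect: "The expected between-group difference (Δ) was three points, with a common standard deviation (σ) of five points".
- Outcome: "we assumed a continuous primary outcome (e.g., postoperative quality of life score or change in serum IL-6". Both examples are listed elsewhere as secondary outcomes.
- Result: "Using the above parameters, 22 participants were required per group, yielding an initial total sample size of 44". With 10% dropout this becomes 50, or 25 per group.

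The section then claims at least 80% power for both primary outcomes and continues: "This sample size also covers the secondary endpoints and no separate calculation was needed".

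Two later sections fix how the secondary endpoints are tested. Data collation (3.9.1) sets the multiplicity rule: "while secondary outcomes and biomarkers will use the False Discovery Rate (FDR) method (FDR = 0.05". Main statistical models (3.9.2) states: "A logistic mixed-effects model will be applied to binary outcomes, such as adverse events (SAE, skin allergy) and intestinal function recovery", with first flatus within 48 h and first defecation within 72 h as the bowel examples.

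The limitations paragraph of the Discussion concedes low power only for subgroup analyses, among which it counts rare adverse events and the Type A versus Type B comparison. It does not mention the secondary endpoints.

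**The concern.** Secondary endpoints need no power calculation, and leaving one out would be no fault. The fault is a positive statement that they are covered. Placed straight after a claim of at least 80% power, the sentence will be taken to mean adequate power.

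The calculation behind it addresses one continuous mean at unadjusted 0.05. It takes no account of the FDR rule and uses no event rate. Nor does its result follow from its own inputs.

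Much of the trial's hypothesis (less inflammation, better intestinal recovery) is tested through secondary endpoints. A reader who trusts the sentence could take a non-significant IL-6, HAMD or flatus result as evidence against an effect that the trial had little chance of detecting.

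**Working it through.** **1. The plan's own figure.** The usual formula is n per group = 2 × [(z for α/2 + z for β) × σ / Δ]². With 1.96, 0.84, σ = 5 and Δ = 3:

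2 × (2.80 × 5 / 3)² = 2 × 21.78 = 43.6, so 44 per group.

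The stated 22 is not reproduced. Leaving out the factor 2 gives 21.8, so 22 matches that slip. The formula as printed, with σ multiplying only the second z-value, gives 8.4 with 0.84, or 15.6 if the β/2 subscript is taken literally (1.28). A one-sided test gives 35. The dropout step is sound: 44 / 0.9 = 48.9, rounded up to 50.

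**2. One continuous secondary endpoint, no adjustment.** The standardised difference is d = 3/5 = 0.6. Noncentral t, two-sided 0.05:

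| n per group | power |
|---|---|
| 22 | 49% |
| 25 | 55% |

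About 22 per group is the relevant number after dropout (50 × 0.9 = 45). The coverage statement therefore fails before any multiplicity rule is applied.

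**3. Adding the FDR rule.** The document names neither the procedure nor the families. Assumptions: Benjamini-Hochberg, normal test statistics and pairwise correlation 0.3. Two family sizes are shown:

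- 12, counted from the Secondary outcome measures section (3.6.2): IL-6, TNF-α, 5-HT, BDNF, bowel sounds, flatus, defecation, GIDS, HAMA, HAMD, SF-36 (once) and PSQI.
- 4, if the biomarkers IL-6, TNF-α, 5-HT and BDNF form their own family.

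Grant the plan exactly 80% power per affected endpoint at unadjusted 0.05. Average simulated power per affected endpoint is then:

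| family | one affected | intermediate | all affected |
|---|---|---|---|
| 12 | 48% | 57% (3), 66% (6) | 75% |
| 4 | 63% | – | 76% |

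At the plan's own d = 0.6 with a family of 12, power runs from one to all affected as follows: about 20–38% with 22 per group and 23–44% with 25.

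The single-effect case is the strictest, because one isolated finding must reach about 0.05/12 = 0.004. The standardised difference giving 80% power (noncentral t) is:

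| n per group | unadjusted 0.05 | isolated effect, family of 12 |
|---|---|---|
| 22 | 0.86 | 1.18 |
| 25 | 0.81 | 1.10 |

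**4. Binary bowel endpoints.** The document gives no event rates, so the control rates below are assumed. Power comes from exact enumeration of the uncorrected chi-square test at unadjusted two-sided 0.05. It simplifies the planned mixed model to one comparison of proportions.

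- 50% v 70%: 26% power with 22 per group, 33% with 25.
- Difference needed for 80% power, control rates 10–60%: about 33–41 points with 22 per group, and about 32–37 points with 25 (for example 30% v 67%, 50% v 85%).

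These figures are before any FDR adjustment.

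**The case against.** Several objections deserve an answer.

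- **The point only follows from the sample-size error.** Partly true: the halved n is the largest single cause, and a corrected calculation would probably rewrite the sentence. But step 3 grants the plan its 80% and the claim still fails, and correcting a formula for means does not size a proportion.
- **The FDR loss depends on how many endpoints respond.** This stands. The Introduction hypothesises broad effects, and if all 12 endpoints respond the granted 80% falls only to about 75%. The isolated-effect case is the worst case, not the trial's hypothesis. The plan's sentence, however, carries no such condition.
- **The family and procedure are assumed.** This also stands. An analysis plan may define smaller families. With a family of 4 the loss is milder, but power still stays below 80%.
- **Flatus and defecation are defined as times; the 48 h and 72 h cut-offs are one analysis of them.** Fair, and the rates used here are assumptions. It limits the binary figures but gives no support to the coverage claim.

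Two stronger readings are tempting. A reader might infer that the FDR rule alone would miss most effects of the size the trial is powered for. It would not: in the granted case average power is 48–75%. Figures below one half throughout arise only at d = 0.6, where the halved n has already cut power to 49–55%. A reader might also infer that the authors will treat null secondary results as showing no effect. The document does not say so; the wording only invites that reading.

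**Conclusion.** The concern holds as an unsupported and incorrect assertion. That the plan's inputs require about 44 per group rather than 22, leaving a single unadjusted continuous test at 49–55% power, rests only on stated figures. That the claim would fail under the FDR rule even from a true 80% rests on an assumed procedure, correlation and family size, and the loss ranges from small (all endpoints affected) to substantial (one affected). That the binary endpoints are not covered follows from the absence of any rate or formula for proportions; the size of the detectable difference rests on assumed rates.

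The documents do not support a claim that the secondary endpoints must be powered. The required correction is to what the plan says about them.

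**What to change.** Delete the sentence in the Sample size estimation section (3.3). State instead that the trial is not powered for the secondary endpoints, that they are reported as estimates with 95% confidence intervals under the FDR rule, and that non-significance will not be read as no effect.

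If detectable effects are quoted, base them on the roughly 22 per group expected after dropout, not on 25. For continuous endpoints that is a standardised difference of about 0.86 at unadjusted 0.05, and about 1.18 for an isolated effect if one FDR family of 12 is assumed. For the binary endpoints it is about 33–41 points at unadjusted 0.05 for control rates of 10–60%. Label the family size and the event rates as assumptions.

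The limitations paragraph of the Discussion should add the secondary endpoints to its remark on low power. The cost is a few sentences and a less favourable stated coverage, with no extra patients, visits or data. The 22 against 44 discrepancy needs its own correction; putting that right would not by itself make the deleted sentence true.
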